## Abstract

**Background:**

The efficacy of peripheral low add multifocal soft contact lenses (SCLs) for suppressing the progression of myopia is controversial. The aim of the on-going present clinical study is to investigate whether or not multifocal SCLs with + 0.50 diopters (D) addition suppress the progression of myopia in myopic elementary school children.

**Design:**

Prospective randomized controlled trial.

**Subjects and methods:**

The study plans to include a total of 100 myopic school children. Target subjects are primary school male and female students with mild to moderate myopia. Children who have eye-related diseases other than myopia are excluded from the study, because they may affect the evaluation of the outcome. Subjects will be randomly assigned to wear daily disposable multifocal contact lenses with + 0.50D addition or daily disposable SCLs. Subjects will wear contact lenses on both eyes and will be observed for 2 years under a double-masked examination. Primary outcome is a change in the axial length over the 2-year period.

**Objectives:**

The purpose of this study is to identify whether or not multifocal SCLs with + 0.5D addition suppress the progression of myopia in myopic elementary school children as compared with standard SCLs.

**Trial registration:**

1. UMIN (University Hospital Medical Information Network) UMIN000027940. Registered on July 21, 2017

2. JRCT (Japan Registry of Clinical Trials) jRCTs052180172. Registered on March 26, 2019

## Introduction

High incidence of myopia in children is a growing problem in Japan. According to a school health statistics survey conducted in 2018 by the Japanese Ministry of Education, Culture, Sports, Science and Technology, “uncorrected decimal visual acuity (VA) less than 1.0” has been reported in 26.7% of children at kindergartens, 34.2% of children at elementary schools, 56.0% of children at junior high schools, and 67.2% of children at high schools [1]. The survey results further revealed that the VA of elementary school children in 2018 is the worst in recorded history.

Myopia has been more frequently found in lower-grade elementary school children. In general, when myopia develops at a younger age, it tends to progress, thus suggesting an increased incidence rate of high myopia in the future [2]. The increased risk of developing complications such as high myopia-associated retinal detachment, glaucoma, myopic macular degeneration, myopic optic neuropathy, or cataracts is of growing concern.

If the progression of myopia can be suppressed during the early school years, a time when VA often rapidly decreases, the quality of life in social activities after adolescence can be well maintained. Furthermore, the risk of blindness caused by vison-threatening diseases is expected to be reduced. Therefore, to establish a method to prevent the progression of myopia during the early school years is a critical social issue. For this issue, various therapies such as eye drops [3, 4], progressive addition glasses [5, 6], and orthokeratology lenses [7, 8], etc., have been tested, and a series of research have been done to establish a therapy for better control of the progression of myopia [9]. A recent study has shown that peripheral add multifocal soft contact lenses (SCLs) suppress the progression of myopia (Fig. 1) [10]. However, there are no published studies showing strong evidence that contact lenses with a low add power suppress the progression of myopia.

**Fig. 1 Fig1:**
[figure not shown]
Design of multifocal soft contact lenses (SCLs) with add power in the periphery areas. It is designed as a + 0.5 diopter progressive-add power from the periphery towards the center

This study is designed to investigate whether or not multifocal SCLs with a relatively low add power suppress the progression of myopia in school children with highly progressive myopia.

### Primary endpoint

The change of axial length (AL) at the end of the observation period compared to the baseline.

### Secondary endpoints

The change of spherical equivalent at each observation time point 0.5, 1, 1.5, and 2 years compared to at baseline.Changes in AL at each observation time point 0.5, 1, and 1.5 years compared to at baseline.Changes in AL and spherical equivalent at each observation time point 0.5, 1, 1.5, and 2 years compared to at the time of enrollment.Observation of the changes in the eyes and extraocular areas by slip-lamp microscopy examination from the start of the study to the end of the observation period (or at the time of study discontinuation).Incidence of adverse events and medical device-related adverse events from the start of the study to the end of the observation period (or at the time of study discontinuation).

### Exploratory endpoints

Subgroup analyses will be performed for patient age, sex, family history, uncorrected distance VA, spherical equivalent power, pupil diameter, lifestyle, and high-order aberrations. These factors could be considered as possible influences on myopia progression.

## Subjects

### Ethical statement

The protocols of this study were approved by the Medical Ethics Review Committee of Kyoto Prefectural University of Medicine, Kyoto, Japan (Approval No. ERB-C-892-2). The study was registered at the University hospital Medical Information Network (UMIN 000027940). After establishing the clinical trials act in Japan, the study was re-approved by the Clinical Research Review Board of Kyoto Prefectural University of Medicine in March 2019 and was registered in the Japan Registry of Clinical Trials (JRCT s052180172). Subjects and their parents/guardians will receive a detailed explanation about the study, and informed consent will be obtained prior to their involvement in the study. The study sponsor is SEED Co., Ltd., yet SEED Co., Ltd. was not involved in any or all of the study design, data collection, management, analysis, and interpretation, the subsequent preparation of the study report, or the decision to submit the final report for publication.

### Study design

This is a prospective therapeutic intervention, multicenter, randomized, double-masked, parallel group comparison study, which will be conducted at the Department of Ophthalmology, Kyoto Prefectural University of Medicine and Department of Ophthalmology, University of Tsukuba, Tsukuba, Japan. The subjects will be independently recruited to compare standard and multifocal SCL (specially controlled medical devices). Authorship was determined with the consent of all authors. This paper will be submitted to the Japanese Journal of Ophthalmology. Since we have no experience with protocol writing, the paper was first written in Japanese and then translated into English. There are no plans for interim and secondary analysis. There are no plans for sharing of the data.

### Subjects

The subjects of this study will be elementary school children with highly progressive mild to moderate myopia. Children who have binocular vision disorder, amblyopia or manifest strabismus, and eye-related diseases other than myopia will be excluded, as they might affect the evaluation of outcomes. Children with any eye disorders in which contact lenses are contraindicated will also be excluded from the study.

#### Inclusion criteria

First to sixth grade male and female elementary school students.Children with worsened VA based on the school examination within the previous year compared to that from the previous examinations.Children who can be examined using cycloplegics.Cycloplegic refraction criteria:Spherical equivalent power within the range of − 1.00D to − 6.00D in both eyes.Difference in the spherical equivalent power between eyes less than 1.50D.Astigmatic power within ±1.50D.Corrected distance VA with glasses 1.0 or higher.Intraocular pressure within the normal range.5)Children who can visit the study site and receive examinations on the scheduled days.6)Children and their parents/guardians who provide signed informed consent to participate in the study.

#### Exclusion criteria

Children with any of the following are excluded:
Binocular vision disorderAmblyopia or manifest strabismusThe difference in the spherical equivalent power with and without cycloplegic 1.50 D or higher in both eyes.Eye-related diseases other than myopiaSystemic diseases that affect vision or refractive errorPast myopia control therapy, such as bifocal glasses, progressive multifocal lenses, orthokeratology lenses, and drug treatment.Children who are determined by investigators to be inappropriate to participate in the study.

### Sample size and randomization

The planned sample size is 50 subjects each at both the Kyoto Prefectural University of Medicine and the University of Tsukuba, i.e., a total of 100 subjects. The sample size is based on the previous published data. Progression of myopia with multifocal SCL and that with standard therapy such as glasses were assumed to be − 0.54D/year and − 0.84D/year, respectively, based on a previous study conducted in USA [11], and standard deviation (SD) was assumed to be 0.66D based on our previous study [12]. Considering that approximately 20% of the subjects would be unevaluable due to study withdrawal, etc., 50 subjects in each group and a total of 100 subjects were determined to be included in this study to detect a between-group significance (alpha = 0.05, two-sided and power = 90%).

Adaptive randomization will be performed to avoid any accidental bias between the two groups. Adaptive stratified sampling will be carried out using the minimization method with genders, grades, and study sites as allocation factors. Randomization is done by an outside clinical research support company. Once consent is obtained, a fax of the case entry is sent and the allocation of the case is sent back.

The meaning of “double-masked” is that both the subjects and the examiners do not know who is in the target group and who is in the control group. An external data center knows whether each case is a subject or a control. The analysis is done in the data center, but in a different department than the allocation.

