## Discussion

Previous studies show that three types of SCL are effective for suppressing the progression of myopia, namely, concentric bifocal lenses [13], extended depth of focus lenses [14], and peripheral add multifocal SCL. The first two have been certified as a CE mark for suppressing the progression of myopia in Europe.

Of peripheral add multifocal SCL, the effectiveness of those with + 2D higher power add has been reported in previous studies [11, 15]. However, they might be unsuitable for elementary school children because of the visual instability. Low add multifocal SCL are commercially available to prevent eyestrain, and they do not lead to the development of presbyopia symptoms such as eye fatigue, eye pain, headache, and so on. The impact of wearing SCL in young children is not yet fully understood.

The potential mechanisms of how the low add multifocal SCL suppress the progression of myopia include a prevention of hyperopic blur on the peripheral retina [16], and decreased accommodation stimuli by the increased multifocality; however, their actions are not yet fully understood in detail. Fujikado et al. shown a significant effect of low add SCL on the AL change but not on the refractive error [17]. Our study is multicenter with expanded number of subjects and longer observation period, to decrease bias. If the present double-masked study confirms significant changes in both AL and refractive error in the low add multifocal SCL group, they might become a standard therapy for myopia correction in school-aged children in Japan.

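### The 90% power is calculated for refraction in dioptres, a secondary endpoint; power for the primary axial-length comparison is not stated and cannot be derived

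*Protocol article*

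**What the plan says.** Under Primary endpoint, the Protocol article names "The change of axial length (AL) at the end of the observation period compared to the baseline". The abstract agrees: "Primary outcome is a change in the axial length over the 2-year period". Refraction comes first in the list under Secondary endpoints: "The change of spherical equivalent at each observation time point 0.5, 1, 1.5, and 2 years compared to at baseline".

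The Sample size and randomization section uses only refraction. It states "Progression of myopia with multifocal SCL and that with standard therapy such as glasses were assumed to be" −0.54 and −0.84 D/year, taken from a US study. It adds an SD of 0.66 D from the group's own earlier study, without saying over what period. Allowing for about 20% unevaluable subjects, it arrives at 50 per group for two-sided alpha 0.05 and 90% power.

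The Discussion reports that an earlier study of a low-add lens had "shown a significant effect of low add SCL on the AL change but not on the refractive error".

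**The concern.** Power belongs to a particular endpoint. It depends on the ratio of the expected difference to the SD on the scale that is analysed. Here that scale is millimetres of axial length, and the article supplies neither quantity on it. The 90% figure sits beside a primary endpoint to which it does not apply, and a reader would naturally take it as the power of the primary comparison.

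The Discussion adds to the concern. By the article's own account, a lens of this class gave a significant result on one of the two endpoints and not on the other. A calculation for refraction therefore cannot be assumed to hold for axial length.

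At stake is the justification of the trial's size for its main question. The validity of the primary test itself is not affected.

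**Working it through.** **Inputs from the article.** 50 per group; about 20% unevaluable, so 50 × 0.80 = 40 evaluable per group; two-sided alpha 0.05 (z = 1.960); power 90% (z = 1.282); progression −0.54 and −0.84 D/year, a difference of 0.30 D/year; SD 0.66 D.

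**Step 1: the plan's own figure, in dioptres.** For two means, n per group = 2 × (1.960 + 1.282)² × (SD/difference)². Power at n per group = Φ(difference / (SD × √(2/n)) − 1.960). At n = 40, √(2/40) = 0.2236.

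| Difference | n per group for 90% | After 20% loss | Power at 40 per group |
|---|---|---|---|
| 0.30 D (annual) | 102 | 128 | Φ(2.033 − 1.960) = 53% |
| 0.60 D (doubled over two years, same SD) | 26 | 33 | Φ(4.066 − 1.960) = 98% |

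A noncentral-t calculation gives 52% and 98%. Neither reading returns 50 per group. Averaging a child's two eyes does not close the gap for 0.30 D: with an assumed between-eye correlation of 0.8, the SD becomes 0.66 × √(1.8/2) = 0.626 D and power is 57%. The nearest match treats 100 eyes per group as independent, with no loss (89.5%). With the stated loss (80 eyes) this falls to 82%, so it is not the stated calculation either.

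**Step 2: what 40 per group can detect on any scale.** Standardised difference for 90% power = (1.960 + 1.282) × √(2/40) = 0.725.

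**Step 3: axial length.** The article gives no difference and no SD, so everything here is assumed, and the ranges are illustrative. SDs are for two-year change, one value per child.

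| Assumed SD (mm) | Detectable at 90% (mm) | Power, true 0.10 mm | Power, true 0.15 mm | Power, true 0.20 mm |
|---|---|---|---|---|
| 0.15 | 0.11 | 85% | 99% | >99% |
| 0.20 | 0.14 | 61% | 92% | 99% |
| 0.25 | 0.18 | 43% | 76% | 95% |
| 0.30 | 0.22 | 32% | 61% | 85% |

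Example: SD 0.20 and difference 0.15 give 0.15 / (0.20 × 0.2236) = 3.354, and Φ(3.354 − 1.960) = 92%.

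The table contains values well below 90% and values well above it. Nothing in the article selects a row or a column.

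**The case against.** The best defence is that axial length and refraction both measure myopia progression, so sizing on refraction is an indirect basis and not an irrelevant one. This stands in part: it would be too strong to say that the dioptre calculation tells us nothing about the primary test. But a relation between endpoints does not carry a power figure across without a stated conversion, and there is none. Nor is the 90% sound enough to act as a proxy, since it does not reproduce on its own scale.

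It could also be said that a journal article condenses a fuller protocol. That does not answer the point. The article does give a complete justification, with means, SD, alpha, power and loss, but for a different endpoint.

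Three stronger readings are tempting, and the documents do not support them:

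- *The trial is underpowered for axial length.* A reader might infer this from the 0.10 mm column alone. At 0.15 or 0.20 mm several assumed SDs exceed 90%. The Discussion also cuts both ways: an effect seen on axial length but not on refraction would, if anything, suggest that axial length could be the more sensitive endpoint. Equally, one significant and one non-significant result, quoted without estimates, do not prove that the effects differ.
- *A null result could not be interpreted.* The confidence interval for the axial-length difference will show which effects are excluded. Prospective power is not needed for that.
- *The earlier low-add study supplies the missing values.* The Discussion says that the present trial has a longer observation period, and it quotes no figures from that study. Two-year values could not be read from it directly.

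**Conclusion.** The point holds. The stated 90% power is calculated for a secondary endpoint, and the power of the primary test is neither stated nor derivable from the article. This follows from setting the endpoint sections beside the sample-size section and rests on no assumed value.

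The firm quantitative result is the 0.72 SD difference needed for 90% power at 40 evaluable per group. The millimetre figures rest on assumed SDs and true differences, and they show only that axial-length power is unknown, not that it is low. The failure of the dioptre calculation to reproduce (53% or 98% at 40 per group) can be checked from the article's own inputs. It is a further reason to redo the paragraph, but the endpoint mismatch would stand without it.

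**What to change.** Keep the sample size and restate the sample-size paragraph for the primary endpoint:

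- Give an assumed two-year axial-length difference and SD in millimetres, with sources. Say whether the SD is per eye or per child, since both eyes enter the model. If a source had shorter follow-up, state the extrapolation.
- Report the resulting power with 40 evaluable per group, and the minimum detectable difference at 90% power (0.72 SD).
- Label the dioptre calculation as applying to change in spherical equivalent. Recompute it with the difference and the SD stated over the same period.
- As the trial is ongoing, date the restatement and say that its assumptions come from outside the trial's own data.

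The cost is one rewritten paragraph and a short calculation. Endpoint, analysis and alpha are untouched. The downside is that the stated power may become less favourable.

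### The 50 per group at 90% power does not follow from the printed inputs: three readings of the SD give about 53%, 82% or 98%, and the text does not say which applies

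*Protocol article*

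**What the plan says.** The sample size paragraph of the Protocol article (Sample size and randomization) prints a full set of inputs and a result:

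- Progression with multifocal and standard correction: "were assumed to be − 0.54D/year and − 0.84D/year, respectively".
- Variability: "standard deviation (SD) was assumed to be 0.66D based on our previous study". No period (one or two years) and no unit (eye or child) is given.
- Loss: "approximately 20% of the subjects would be unevaluable due to study withdrawal".
- Error rates: "alpha = 0.05, two-sided and power = 90" per cent.
- Result: "50 subjects in each group and a total of 100 subjects were determined to be included in this study to detect a between-group significance".

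The Abstract says that children "will be observed for 2 years under a double-masked examination". Under Primary endpoint, the outcome is change in axial length. Change in spherical equivalent, the scale of the calculation, is listed under Secondary endpoints. Under Data analyses, both eyes enter a mixed model with the child as a random effect.

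**The concern.** A reader who puts the printed inputs into the usual two-sample formula does not get 50 per group. The difference is expressly per year, the SD has no period, and the trial lasts two years, so difference and SD may not be on the same time base. The answer changes a great deal with the period chosen.

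The 90% is the article's only statement of power. Readers will use it to judge how much a non-significant result tells them, and they cannot do so if the figure does not follow from its assumptions. The calculation is also in diopters while the primary endpoint is axial length, so the 90% cannot be read as the power of the primary comparison even once the arithmetic is repaired.

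**Working it through.** **Inputs** (all from Sample size and randomization): difference 0.84 − 0.54 = 0.30 D per year, or 0.60 D over two years if the rate is constant; SD 0.66 D; two-sided alpha 0.05 (z = 1.960); power 90% (z = 1.282); 50 per group less 20% = 40 evaluable per group.

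**Formulas** (normal approximation, child as unit):

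- Evaluable per group: n = 2 × (1.960 + 1.282)² × (SD/difference)². Enrolled per group: n / 0.8.
- Power: Φ(difference / (SD × √(2/40)) − 1.960), with √(2/40) = 0.2236.

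**Attempt to reproduce the stated figure, inputs as printed (0.30 D, SD 0.66 D).** n = 2 × 10.51 × (2.2)² = 101.7, so 102 evaluable and 102/0.8 = 127.5, so 128 enrolled per group. The plan has 50. With 40 evaluable, power is Φ(0.30/0.1476 − 1.960) = Φ(0.073) = 52.9%. With all 50 evaluable it is 62.3%. The stated figure is not reproduced.

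**0.66 D as an annual SD, scaled to two years (0.60 D).** Assuming independent years, SD = 0.66 × √2 = 0.93 D. n = 51 evaluable, 64 enrolled per group. With 40 evaluable, power is Φ(0.60/0.2087 − 1.960) = Φ(0.915) = 82.0%. If a child's rate were instead the same in both years, the SD would double to 1.32 D and power would return to 52.9%.

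**0.66 D as the SD of a two-year change of 0.60 D.** n = 2 × 10.51 × (1.1)² = 25.4, so 26 evaluable and 33 enrolled per group. With 40 evaluable, power is Φ(0.60/0.1476 − 1.960) = Φ(2.106) = 98.2%.

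| Reading | Difference | SD | Evaluable / enrolled per group for 90% | Power, 40 per group | Same, t-test |
|---|---|---|---|---|---|
| As printed | 0.30 D | 0.66 D | 102 / 128 | 52.9% | 51.9% |
| Annual SD scaled to two years | 0.60 D | 0.93 D | 51 / 64 | 82.0% | 81.0% |
| SD of two-year change | 0.60 D | 0.66 D | 26 / 33 | 98.2% | 98.0% |

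**Working backwards.** For 90% with 40 per group, the SD would have to be 0.30/(3.242 × 0.2236) = 0.41 D for a difference of 0.30 D, or 0.83 D for 0.60 D. Neither is printed.

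**Detectable difference.** With 40 per group and 90% power: 3.242 × 0.2236 = 0.725, so about 0.72 SD, whatever the scale.

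**The case against.** **The SD's period may be given elsewhere.** The article condenses a fuller protocol, and the SD comes from an earlier study that is not shown. Silence on the period would not by itself be an error. But the article prints both inputs and result, and they disagree on each of the three readings.

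**Two eyes per child raise power.** Averaging two eyes multiplies the SD by √((1 + r)/2), where r is the between-eye correlation. The documents give no r. At 0.30 D with SD 0.66 D and 40 children, power is 65% for an assumed r of 0.5, 57% for 0.8 and 55% for 0.9. Even fully independent eyes (80 per group) give 82.0%. One can reach 90% by stacking two unstated assumptions: the 0.93 D reading together with r of about 0.57, since 0.93 × √(1.57/2) is about 0.83 D. That shows a route exists, not that the plan took it. A one-sided test brings the 0.93 D reading to 89.1%, but the plan is two-sided.

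**The trial is underpowered.** A reader might infer this from the 53%. The documents do not support it: the trial runs two years and its primary endpoint is change at the end of observation, so a two-year calculation is at least as natural, and one such reading gives 98%. Nor is any of these figures the power of the axial-length comparison.

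**The origin of the 100.** A reader might infer that eyes were counted as children, because 100 independent eyes per group give 89.5%, or that a per-group number was taken as the total, because 102 is close to 100. The first match needs the stated 20% loss to be ignored; with it, power is 82.0%. The second compares a number before loss with an enrolled total; after loss it is 128. The model under Data analyses also does not treat eyes as independent. How the 100 was reached is unknown and does not matter to the point.

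**Conclusion.** The point holds in a limited form. The stated 50 per group at 90% power does not follow from the stated difference, SD, loss and two-sided alpha. With 40 evaluable children per group, power for refraction is about 53%, 82% or 98%, depending on what the 0.66 D describes. The 82% assumes independent years, both two-year readings assume a constant annual difference, and all three take the child as the unit.

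The fault is a power claim that cannot be reproduced and an SD without a period or unit. It is not a demonstrated shortfall: the possible values lie on both sides of 90%, and they concern a secondary endpoint.

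**What to change.** Revise the sample size paragraph as follows:

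1. State whether 0.66 D is the SD of a one-year or a two-year change, and whether it is per child or per eye.
2. Put the difference and the SD on the same period. If an annual SD is scaled, say how.
3. Recompute at child level with 40 evaluable per group, and replace the 90% with the result. If eyes are averaged, state the between-eye correlation assumed.
4. Label the result as power for change in refraction, a secondary endpoint, and not for axial length.
5. Add that 40 evaluable children per group detect a difference of about 0.72 SD with 90% power (two-sided alpha 0.05). This applies to either endpoint.

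The cost is the wording of one paragraph. The downside is that the stated power may become less favourable. No change to enrolment is asked.
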